#### Title of the study:

Self-management of type 2 diabetes using a co-designed text based mobile health (mhealth) intervention in Nepal: a randomized controlled trial

#### Summary of the proposed research protocol (within 200 words)

The overall burden of diabetes is rising, especially in low and middle-income countries such as Nepal. In Nepal, access to diabetes care varies by socio-economic and geographical factors, posing significant challenges to prevention and control. Self-management plays a crucial role in the prevention and control of diabetes. Mobile health (mHealth) technology is increasingly popular for managing chronic diseases, demonstrating its feasibility, acceptability, and effectiveness in enhancing health outcomes and encouraging behavior change. However, its impact on improving self-management among people with type 2 diabetes in Nepal remains unexplored. This randomised controlled trial aims to evaluate a 6-month text based mhealth intervention that support self- management among people with type 2 diabetes in Nepal. The primary outcome includes change in HbA1c at 6 months. Secondary outcomes include behaviour change for diabetes self-management activities, self-efficacy, perceived support, diabetes related stress, quality of life and acceptability of the intervention acceptability. In addition, an economic evaluation will be conducted using a patient perspective. Primary and secondary outcomes will be summarized descriptively, and comparisons will be made using chi-square tests for categorical data and independent sample t-tests for continuous data using SPSS. A cost-effectiveness analysis will be conducted using the incremental cost-effectiveness ratio (ICER).

#### DETAIL OF THE STUDY

**B.1. BACKGROUND:**

The number of people living with diabetes has increased globally and is on rapid rise among low and middle income countries (LMICs) ([WHO, 2021](#_ENREF_52)). In 2021, there were 537 million people living with diabetes and this number is expected to rise to 643 million by 2030 and 783 million by 2045 ([IDF, 2021](#_ENREF_21)). More than three in four adults with diabetes are living in LMICs. Diabetes accounted for 6.6 million deaths in 2021 ([IDF, 2021](#_ENREF_21)) and is a major cause of blindness, kidney failure, heart attack, stroke and lower limb amputation ([WHO, 2021](#_ENREF_52)). Following the global trend, the prevalence of diabetes has been increasing in Nepal ([Dhungana et al., 2021](#_ENREF_9); [Shrestha et al., 2021](#_ENREF_42)). The International Diabetes Federation (IDF) estimated a prevalence of 8.7% among Nepalese population and the proportion is to rise to 9.4% by 2045 ([International Diabetes Federation, 2021](#_ENREF_22)).

The burgeoning burden of disease may place serious challenges on the resource constrained national health system due to complications resulting from the disease, coupled with issues around service availability & readiness and limited awareness among the people living with diabetes ([Ghimire et al., 2020](#_ENREF_16); [Gyawali et al., 2016](#_ENREF_19)).

Access to care is of utmost importance for people with diabetes in the course of their disease however, the availability and utilisation of diabetes care services vary across socio-economic and geographical distribution indicating challenges in accessing the diabetes care services ([Upreti et al., 2016](#_ENREF_49)). WHO STEPS survey Nepal 2019 reported about three-fourth (73.5%) of the people were not aware of their raised blood sugar. Despite being aware of their condition, about 6% were not on treatment. Similarly, only 70% of adults with raised blood sugar reported compliance to medications to control their blood sugar ([Dhimal M et al., 2020](#_ENREF_8)). In addition, public health facilities in Nepal are not ready to deal with the increasing burden of NCDs including diabetes in terms of qualified health staff, training, availability of equipment and medicines as well as availability of diabetes services in general ([Adhikari et al., 2023](#_ENREF_4); [Ghimire et al., 2020](#_ENREF_16); [Huda et al., 2021](#_ENREF_20)).

Early diagnosis, treatment and self-management are essential for the prevention and control of the disease ([WHO, 2021](#_ENREF_52)). Self-management refers to the activities and behaviour undertaken by the individuals to control and treat their conditions to improve their health outcomes with support from family members, friends and relatives and in consultation with health service providers ([Powers et al., 2017](#_ENREF_39)). The American Association of Diabetes Educators (AADE) has identified seven self-care behaviours for successful and effective self-management of diabetes as healthy coping, healthy eating, being active, taking medication, monitoring, reducing risks and problem solving ([AADE, 2020](#_ENREF_1)). Self-management has been proved to be cost effective through reduction in hospital admissions and health care costs ([Panagioti et al., 2014](#_ENREF_38)). Besides, it is shown to improve HbA1c level and has a positive effect on other clinical, psychosocial, and behavioural aspects of diabetes along with improvement in quality of life by reducing onset and/or advancement of diabetes complications ([Powers et al., 2017](#_ENREF_39); [Sukartini et al., 2023](#_ENREF_46)).

With the development of technology, the application of mobile health (mhealth) is becoming increasingly popular in the self-care of chronic diseases ([Kang & Park, 2016](#_ENREF_25)). mhealth interventions have been proved to be a therapeutic strategy that could improve the diabetes management despite their economic status ([Fadilah et al., 2020](#_ENREF_12); [Johnston et al., 2018](#_ENREF_24); [Kitsiou et al., 2017](#_ENREF_26); [Lu et al., 2019](#_ENREF_28); [Mao et al., 2020](#_ENREF_30); [Wang et al., 2020](#_ENREF_50); [Xiong et al., 2018](#_ENREF_54)). According to the National Population and Housing Census report 2021 ([CBS, 2021](#_ENREF_6)), about three-fourth (73%) of the households have at least some form of smartphone penetration and 37.9% household with internet access in Nepal.

**STATEMENT OF THE PROBLEM/ RATIONALE/ NEED OF THE STUDY:**

In the resource limited countries like Nepal, mhealth technology can be a cost-effective approach to deliver care and improve the health outcomes. There are studies demonstrating the feasibility, acceptability ([Bhandari et al., 2022](#_ENREF_5); [Ni et al., 2020](#_ENREF_36)) and even effectiveness ([Bhandari et al., 2022](#_ENREF_5)) of mhealth in improving the health outcomes for hypertension in Nepal ([Bhandari et al., 2022](#_ENREF_5); [Ni et al., 2020](#_ENREF_36)). There is also existing evidence of mhealth as an effective means to communicate health related information and supporting positive behaviour change in a short period of time ([Tuitui et al., 2022](#_ENREF_48)). Despite availability of body of evidence on acceptability of mhealth in improving service utilization and health outcomes for chronic conditions, the application of behaviour change interventions through mhealth for self-management of diabetes is yet to be evaluated.

**OBJECTIVES OF THE RESEARCH:**

***General objective (s):***

This study aims to develop and evaluate a text based mhealth intervention that support self-management in people with Type 2 Diabetes using a co-designed approach

***Specific objective(s):***

1. To identify the barriers and facilitators in adoption of text based mhealth intervention in self-management of type 2 diabetes
2. To explore the perspective of service providers and end users on use of text based mhealth for self-management of type 2 diabetes
3. To develop a theory based contextual text based mhealth intervention that support self-management in people with type 2 diabetes
4. To determine the effectiveness, cost-effectiveness and acceptability of text based mhealth intervention in supporting self-management in people with type 2 diabetes

**STUDY SITE AND JUSTIFICATION:**

The study will be conducted in Dhulikhel hospital of Kavrepalanchowk district, Nepal. Dhulikhel hospital is a tertiary level hospital, catering comprehensive and quality health services to about 2.5 million people having diverse characteristics in terms of ethnicity, residence, socio-economic status and health conditions with particular focus on rural and unserved population.

**METHODS/ METHODOLOGY:**

***Mixed Research Design***

We will conduct a qualitative study to explore perspectives of service providers and users on use of text based mhealth to support self-management among people with type 2 diabetes together with identifying potential barriers and facilitators for implementation of the intervention. The study population will include people with type 2 diabetes aged 18 years and above. We will further include service providers involved in the delivering diabetes care services. We will collect qualitative data using In-Depth Interview (IDI), and Focused Group Discussion (FGD).

Further to this, the study will include a 6-month text-based mhealth intervention and employs a two-arm parallel group randomised control trial to evaluate the effectiveness, cost effectiveness and acceptability of a text-based mhealth intervention in improving self-management among people with type 2 diabetes.

***Study design:***

This study is a 6 month text-based mhealth intervention and employs a two-arm parallel group randomised control trial to evaluate the effectiveness and acceptability of a text-based mhealth intervention in improving self-management among people with type 2 diabetes in Dhulikhel Hospital, Kavrepalanchowk, Nepal.

***Study Variables***

1. Socio-demographic factors: Age, sex, ethnicity, religion, marital status, education and occupation
2. Health related characteristics: Family history, individual co-morbid condition and complications of diabetes
3. Self-efficacy: Diabetes Self Efficacy Scale (DSES) is an 8-item with a scale ranging from 1 (not at all confident) to 10 (totally confident). The score for the scale is the mean of eight items where higher number indicated higher self-efficacy ([Ritter et al., 2016](#_ENREF_44)). This scale is found to have good internal consistency and test-retest validity ([Kerari, 2023](#_ENREF_30); [Mankan et al., 2017](#_ENREF_34)) and have been modified and used in Nepalese context ([Dwa & Panthee, 2021](#_ENREF_12)).
4. Perceived support: Multidimensional Scale of Perceived Social Support is a 12-item, 7-point Likert scale (1 as very strongly disagree to 7 as very strongly agree) to assess perceived support from family, friends and significant other ([Zimet et al., 1988](#_ENREF_60)). Nepalese version of this scale is found to have good construct validity and reliability ([Tonsing et al., 2012](#_ENREF_51)).
5. Diabetes related stress: Diabetes Distress Scale consists of 17 questions in total: Emotional burden (5 questions), Physician related distress (4 questions), Regimen related distress (5 questions) and Interpersonal distress (3 questions). Responses for the question ranges from 1 (slight problem) to 6 (very serious problem). Mean is calculated for each subscale. This scale is found to be valid and reliable tool to assess distress among people with type 2 diabetes in context similar to Nepal ([Akter et al., 2022](#_ENREF_3)).
6. Quality of life: WHOQOL- BREF consists of 26 items across four domains: physical, psychological, social and environment including the questions on overall quality of life and general health. The score ranges from 1 to 5 on a response scale. Higher scores denote higher quality of life ([WHO, 1998](#_ENREF_56)). This tool is found have good internal consistency and validity in assessing the quality of life of people across different cultures ([Almarabheh et al., 2023](#_ENREF_4); [Kalfoss et al., 2021](#_ENREF_27); [Sreedevi et al., 2016](#_ENREF_49)) including Nepal ([Joshi et al., 2023](#_ENREF_26)).We will use Nepali version of WHOQOL-BREF.
7. Self-care activities: Revised scale of Summary of Diabetes Self Care Activities measure consists of core set of 11 items from Summary of Diabetes Self Care Activities measure and additional 14 questions ([Toobert et al., 2000](#_ENREF_52)). It is found to be valid and reliable tool for assessing self-care behavior among adults with diabetes ([Jalaludin et al., 2012](#_ENREF_24)).
8. Economic evaluation: Economic evaluation of the intervention will be done using the cost information obtained at baseline and follow up (after 6 month) including the cost of development and delivery of mhealth intervention and Quality-adjusted Life Years (QALYs).
9. Acceptability of intervention: Acceptability of the intervention will be measured through “Yes” or “No” questions on usefulness, appropriateness, sharing, learning and support in diabetes management and behavior change ([Dobson et al., 2016](#_ENREF_11)).

***Expected outcomes of the research***

This study aims to evaluate and determine acceptability of a text based mhealth intervention that support self-management in people with type 2 diabetes in Nepal. If proven to be effective, it can be integrated into routine care for people with type 2 diabetes to improve self-management for their condition.

**STUDY POPULATION AND SAMPLE**

***Participants/ study population:***

The study population include people with type 2 diabetes visiting the diabetic clinic at Dhulikhel hospital and service providers who are directly involved in providing care for people with type 2 diabetes

***Selection criteria:***

***Inclusion criteria:***

Inclusion criteria for the study include a. adults aged 18 years and above b. clinical diagnosis of type 2 diabetes c. participant who have a mobile phone and is able to read the message on their own or with the help of family members.

***Exclusion criteria:***

Participants are not eligible if they are a. not physically or mentally able, not able to provide consent b. pregnant in case of female.

***Sampling method/ technique:***

Each person visiting the diabetic clinic in Dhulikhel hospital will be screened for eligibility. Those meeting the eligibility criteria will be approached to participate in the study. The participants will be recruited consecutively until the target sample size is reached.

***Sampling Unit:***

Individual

***Sample size determination:***

**Qualitative:** The number of study participants for IDI will depend on representation of diverse individuals particularly age and gender; and theory of saturation. The availability of study participants will determine the number of FGDs and may range from 2 to 4 with 6 to 8 participants in each FGD.

**Quantitative:** Considering a mean difference (standard deviation) in HbA1c to be 0.86 (±1.08) in the intervention group and 0.18 (±1.53) in the control group from baseline to after 6 months’ intervention ([Islam et al., 2015](#_ENREF_23)) a sample size of 122 was calculated initially to achieve a power of 80% at 5% level of significance. Adjusting to 20% attrition rate, the sample size was increased to 153. To consider equal number of participants in each group, we plan to include a total of 154 participants with 77 participants in each arm.

***Data Collection Procedure:***

Formative research: We will identify potential participants for formative research which includes people with type 2 diabetes and health service providers in coordination with the team from Dhulikhel hospital. The participants will be approached by the lead researcher and inform about the objective of the study through the information sheet. Those who provide written consent to participate in the study will be recruited and involved in the study for interview and discussion.

Screening of participants for RCT: We will screen each person visiting the diabetic clinic in Dhulikhel hospital for the eligibility. Those meeting the eligibility criteria will be approached to participate in the study.

Written Informed consent for RCT: Those who meet the inclusion criteria and agree to participate in the study will be provided with the information sheet that contains information about the objective of the study, procedures, duration, potential risk and benefits, confidentiality, their voluntary participation and frequency of participation in the study. The participants will be provided an opportunity to ask questions and clarifications on anything they are not sure about and presented with a consent form to review and sign if they agree to participate.

A simple randomization technique ([Kang et al., 2008](#_ENREF_29)) will be used to assign participants to either intervention or control group on 1:1 basis. Concealment of allocation will be done using Sequentially numbered, opaque, sealed envelope (SNOSE) technique ([Sil et al., 2019](#_ENREF_46)).An open-source random number sequence generator (random.org) will be used to generate random numbers in two columns (77 each) from 1 to 154 indicating column one for intervention group and column two for control group ([random.org](#_ENREF_41)). The generated numbers in column one and column two will be kept in sequential order in two separate opaque sealed envelopes with a number labelled on outside. The lead researcher will generate the random number and prepare the envelopes while the research assistant will assign the participants to intervention or control group accordingly. A face to face interview will be conducted with people with type 2 diabetes using a structured questionnaire which includes questions related to self-efficacy, perceived support, stress, quality of life, self-care behavior and cost (disease related and development and delivery of intervention) including questions on acceptability of the intervention at follow up. Data will be collected at baseline and 6 months after the intervention.

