***Potential Biases***

There may be a chance of selection bias while assigning participants to intervention or control group. To minimize this, a simple randomization technique (Kang et al., 2008) will be used to assign participants to either intervention or control group on 1:1 basis. Concealment of allocation will be done using Sequentially numbered, opaque, sealed envelope (SNOSE) technique (Sil et al., 2019). An open-source random number sequence generator (random.org) will be used to generate random numbers in two columns (77 each) from 1 to 154 indicating column one for intervention group and column two for control group (random.org). The generated numbers in column one and column two will be kept in sequential order in two separate opaque sealed envelopes with a number labelled on outside. A statistician will generate the random number and prepare the envelopes while the research assistant will assign the participants to intervention or control group accordingly.

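### The envelope procedure described (two arm lists in two envelopes) is not the SNOSE technique the protocol names, and the protocol contradicts itself on who prepares it

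*Protocol*

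**What the plan says.** Under Data Collection Procedure, the protocol states: "Concealment of allocation will be done using Sequentially numbered, opaque, sealed envelope (SNOSE) technique". The next sentence uses an online generator to "generate random numbers in two columns (77 each) from 1 to 154 indicating column one for intervention group and column two for control group". The columns are then stored as follows: "The generated numbers in column one and column two will be kept in sequential order in two separate opaque sealed envelopes". Potential Biases repeats the procedure, saying that the numbers "will be kept in sequential order in two separate opaque sealed envelopes with a number labelled on outside", and offers it as the safeguard against selection bias.

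On roles, Data Collection Procedure says: "The lead researcher will generate the random number and prepare the envelopes". Potential Biases gives the same task to a statistician. In both sections the research assistant makes the assignments. The consent section allows either the lead researcher or the research assistant to obtain consent.

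Both sections call the method simple randomisation ("A simple randomization technique") while fixing 77 participants per arm.

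**The concern.** SNOSE works because each envelope carries one allocation, so opening it discloses nothing about the next participant. Two envelopes that each hold a whole arm's numbers lack that property. Sealing and opacity protect the list only until the first opening.

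Concealment carries much of the weight in this trial. Recruitment is consecutive in one clinic (Sampling method/technique). The protocol accepts that neither participants nor outcome assessors can be blinded (Limitations of the study). The planned comparison is an independent-sample t-test (Plan for data analysis), which does not adjust for differences in who was enrolled. Someone who obtains consent and knows the next assignment can influence who joins, when, and in what order.

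The split of roles is a second route to the same problem. If the lead researcher generates the list and also obtains consent, a recruiter could know the sequence in advance however the envelopes are built.

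**Working it through.** **1. List length.** Sample size determination gives HbA1c changes of 0.86 (SD 1.08) and 0.18 (SD 1.53), 80% power and a 5% level (two-sided assumed).
- Difference: 0.86 − 0.18 = 0.68.
- Common SD: √[(1.08² + 1.53²)/2] = √1.75365 = 1.324.
- Normal approximation: n per arm = 2(1.96 + 0.8416)² × 1.75365/0.68² = 59.5, so 60 per arm and 120 in total.
- Two-sample t-test: 60.5, so 61 per arm and 122 in total, which is the protocol's figure.
- Attrition: 122/(1 − 0.20) = 152.5, so 153, made even at 154, or 77 per arm.

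The stated 122, 153 and 154 are reproduced. The list has 154 entries, and this point does not alter the sample size.

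**2. What one opening discloses, as written.** The two columns partition 1 to 154. Opening either envelope shows 77 numbers, and the remaining 154 − 77 = 77 belong to the other arm. Disclosed: 154 of 154, or 100%.

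**3. What one opening discloses under SNOSE.** One allocation. Past assignments and the fixed 77:77 total still allow some guessing. In a simulation of 20,000 lists, always guessing the arm with more places left was right 84.3 times in 154, or 84.3/154 = 55%.

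**4. Roles side by side.**

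| Task | Data Collection Procedure | Potential Biases | Consent section |
|---|---|---|---|
| Generate list, prepare envelopes | Lead researcher | Statistician | – |
| Assign participants | Research assistant | Research assistant | – |
| Obtain consent | – | – | Lead researcher or research assistant |

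Under the first column, a person who may obtain consent also makes the list. Under either column, the person who assigns may obtain consent.

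**5. Label.** Simple randomisation of 154 gives exactly 77:77 with probability C(154,77)/2¹⁵⁴ = 0.064, with a 95% range of 65 to 89 per arm. Fixing 77 per arm is therefore a random allocation rule.

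**6. Illustration only.** Suppose steered enrolment shifted the between-arm difference in HbA1c change by b. With 61 completers per arm, SE = 1.324 × √(2/61) = 0.240, and type I error = P(|Z + b/0.240| > 1.96).

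| Assumed b (HbA1c points) | Type I error |
|---|---|
| 0 | 5% |
| 0.1 | 7% |
| 0.2 | 13% |
| 0.3 | 24% |

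The values of b are assumptions; nothing in the protocol supplies them.

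**The case against.** **The wording may be loose.** SNOSE is named, and the envelopes are "kept in sequential order in two separate opaque sealed envelopes with a number labelled on outside". An outside number has little use on an envelope that holds a whole arm list, so individually numbered envelopes may be meant. This stands as a caveat on what staff will do. It does not clear the text: two envelopes are described in two sections, and nowhere is one envelope per participant described. Two stacks of envelopes sorted by arm would also reveal the arm.

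**Timing is not stated.** The Work plan puts recruitment and baseline data collection in July–August 2025 and intervention delivery from September 2025. If envelopes were opened only once all participants had been enrolled and numbered, no later enrolment decision would be exposed and the harm would largely vanish. The protocol does not say this; it does not state rolling allocation either. The disclosure result is therefore conditional.

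**Consecutive recruitment limits discretion.** Every clinic attender is to be screened, eligible people are to be approached, and eligibility is broad. This narrows the room for steering but does not remove it, because consent conversations and their timing remain open to influence.

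**Adjustment could help.** Baseline HbA1c is measured, so adjusting for it could remove part of an imbalance. The unmeasured part would remain. It would be too strong to say that no analysis could help at all.

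**The label is harmless.** A 77:77 allocation rule is valid and biases nothing. This is accepted, and the label adds nothing to the seriousness of the point.

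**Conclusion.** The concern holds as a contradiction in the written plan. The procedure described in two sections is not the technique both sections name, and no other part of the protocol corrects it. Followed literally during ongoing consecutive recruitment, the first opening discloses all 154 allocations to a research assistant who may also obtain consent. The sections also disagree on whether the lead researcher or a statistician makes the list, and the consent section lets the lead researcher recruit.

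This rests on two assumptions: that the two-envelope wording is meant literally, and that envelopes are opened before recruitment ends.

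A reader might infer that allocation in this trial is certainly unconcealed, or that its type I error will be 7% to 24%. The protocol supports neither. The first needs both assumptions to be true. The second only restates an assumed bias of 0.1 to 0.3 HbA1c points. The written procedure should still be corrected before the first participant is allocated, because concealment is the main protection against selection bias in an unblinded trial and the correction is cheap.

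**What to change.** In both Data Collection Procedure and Potential Biases:

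1. Replace the two envelopes with 154 individually numbered, opaque, sealed envelopes, one allocation in each.
2. Name one preparer, the statistician or another person with no part in recruitment or consent, and reconcile the two sections and the consent section accordingly. Single-allocation envelopes alone are not enough if the person who makes the list can also obtain consent.
3. State that envelopes are opened strictly in order, each only after that participant's consent and baseline measurements are complete.
4. As a minor wording point, call the method a random allocation rule with 77 per arm in place of simple randomisation.

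The cost is 154 envelopes, a preparer independent of recruitment (a statistician is already named in Potential Biases), and edits to the two sections with a check against the consent section. The sample size stays at 154.

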***Limitations of the study (if any):***

The study is limited to people who are able to use mobile phones therefore may owe to digital literacy bias. The intervention does not allow blinding of the participants and those assessing the outcomes.

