***Who will obtain the consent from the study participants?***

Lead researcher or research assistant

***Is there anything being withheld from the research participants at the time the informed consent is being sought? Mention “YES” or “NO***

*No*

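### The protocol names two different people as maker of the allocation list, and one of them is also permitted to take consent, which can defeat allocation concealment

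*Protocol*

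**What the plan says.** Four statements in the protocol bear on concealment.

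- **Who makes the list.** Data Collection Procedure: "The lead researcher will generate the random number and prepare the envelopes". Potential Biases, describing the same procedure: "A statistician will generate the random number and prepare the envelopes".
- **Who assigns.** Both sections give this to the research assistant: "the research assistant will assign the participants to intervention or control group accordingly".
- **Who consents.** The consent section asks who obtains consent from study participants and answers "Lead researcher or research assistant". It does not separate the formative study from the trial.
- **How allocation is concealed.** "Concealment of allocation will be done using Sequentially numbered, opaque, sealed envelope (SNOSE) technique". The numbers in the two columns, one column per arm, "will be kept in sequential order in two separate opaque sealed envelopes with a number labelled on outside".

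The limitations section adds: "The intervention does not allow blinding of the participants and those assessing the outcomes".

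**The concern.** Concealment requires that whoever brings a patient into the trial cannot know the next allocation. If the lead researcher writes the list and also takes consent, that condition fails, however opaque the envelopes are. Someone who knows the list can present the trial more or less persuasively, or lean on the judgement in the exclusion criterion about physical and mental ability.

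The stakes are higher than usual because participants and outcome assessors are unblinded, which leaves concealment as one of the main remaining protections. The protocol's planned comparison for continuous outcomes is an independent-samples t-test, which would not correct an imbalance created at enrolment. Potential Biases itself names selection bias at assignment as the threat this procedure is meant to reduce.

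**Working it through.** **Comparison of the text**

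1. List-maker: lead researcher (Data Collection Procedure) or statistician (Potential Biases). The task is the same, and no other section resolves the difference.
2. Consent-taker: lead researcher or research assistant (consent section), with no exception for the trial.
3. Taking Data Collection Procedure with the consent section, the list-maker is one of the two people permitted to consent. No section bars a list-holder from screening, approaching or consenting trial participants.
4. Taking Potential Biases with the consent section, the lead researcher no longer makes the list, so that overlap disappears.
5. Two features are the same in both versions. The research assistant assigns and may also consent. The envelopes are described as two, one per column and so one per arm. Read literally, this is not one numbered envelope per participant, which is what the named technique implies. Once an arm-level envelope is opened, every number in that arm is visible.

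**Illustrative arithmetic (the point does not depend on it)**

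Inputs from Sample size determination: changes of 0.86 (SD 1.08) and 0.18 (SD 1.53), 80% power, 5% significance (taken as two-sided, since sidedness is not stated), 20% attrition.

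- Planned difference = 0.86 − 0.18 = 0.68. Pooled SD = √((1.08² + 1.53²)/2) = 1.324.
- Plan's own figure: the t-based calculation gives 61 per arm (power 0.803; 60 per arm gives 0.797), so 122 in total, as stated. 122/0.80 = 152.5, rounded up to 153, then 154 for equal arms. This reproduces the protocol.
- Standard error at 61 per arm = 1.324 × √(2/61) = 0.240.
- With no true effect and a bias b in the mean difference, two-sided type I error ≈ P(Z > 1.96 − b/0.240) + P(Z < −1.96 − b/0.240).

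| Assumed b (HbA1c points) | Type I error |
|---|---|
| 0 | 0.050 |
| 0.1 | 0.070 |
| 0.2 | 0.133 |
| 0.3 | 0.240 |

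The values of b are assumptions; nothing in the protocol supports a particular one. The largest is 0.3/0.68 = 44% of the planned effect.

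**The case against.** A reader might infer that the lead researcher will in fact consent trial patients while knowing the list, so that concealment is already lost. The protocol does not say so. The consent answer says *or*, and it covers the formative interviews and focus groups as well as the trial. The one sentence that has the lead researcher approach people, "The participants will be approached by the lead researcher", belongs to the formative research paragraph and is no evidence about the trial. A coherent reading is that the lead researcher consents formative participants and the research assistant consents trial participants.

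There are also partial safeguards. Every clinic attender is to be screened, those eligible are to be approached, recruitment is consecutive, and in both versions someone other than the list-maker assigns. These limit discretion.

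This objection stands against certainty but not against the point. The safeguards do not stop a person who knows the list from influencing consent or an eligibility judgement. The protocol permits the overlap, and the contradiction over who makes the list remains on any reading.

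A second tempting inference is that choosing the statistician settles the matter. It does not, because the two-envelope layout and the research assistant's dual role are common to both versions.

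**Conclusion.** The contradiction over who generates the numbers and prepares the envelopes is plain in current text and must be resolved. Under the Data Collection Procedure version, a person who knows the allocations may recruit and consent trial participants, which can defeat concealment. The supportable wording is *may* and *can*: the overlap is allowed, not stated to occur.

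The size of any resulting bias cannot be derived from the protocol. The 7% to 24% range shows what an assumed bias of 0.1 to 0.3 points would do at 61 per arm. It does not estimate the effect of this wording and should not be cited as such.

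**What to change.** 1. In Data Collection Procedure, name the statistician, as Potential Biases already does. The statistician generates the list, prepares and seals the envelopes, and holds the list.
2. In the consent section, state that nobody with access to the list may screen, consent or enrol trial participants. This must be explicit for the statistician too, since the protocol does not say that this person has no contact with participants.
3. In both sections, replace the two arm-level envelopes with one sequentially numbered, opaque, sealed envelope per participant (154 in all), opened by the research assistant only after consent and baseline data are complete. The research assistant can then still consent and assign without being a list-holder. With arm-level envelopes, item 2 would exclude the research assistant once an envelope was opened.

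The cost is small: edits to three sections and the preparation of 154 envelopes. No new role is needed, because a statistician is already named. The work plan puts recruitment in July and August 2025. If it has already taken place, the sponsor should instead document who generated the list, who took consent and how the envelopes were used.
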